### Biochemical assessments

After 12 h of fasting, a 10-mL venous blood sample will be taken from each patient at the study baseline and end of trial. Total CBC, hemoglobin concentrations, and hematocrit will be measured by a cell counter. Erythrocyte sedimentation rate will be measured using the Wintergreen method. Then, serum will be isolated from the whole blood and will be stored at − 70 °C until further analysis. Serum concentrations of inflammatory cytokines, including high-sensitivity C-reactive protein (hs-CRP), Tumor necrosis factor-α (TNF-α), interleukin-1β (IL-1β), and interferon gamma (IFN-γ) will be measured by the enzyme-linked immunosorbent assay (ELISA) commercial kits. Earlier studies have shown that hs-CRP, TNF-α, IL-1β, and IFN-γ concentrations are positively associated with severity of IBD, particularly UC [33].

### Gut microbiota and fecal calprotectin

From each individual, 10-g stool sample will be taken to examine gut microbiota and fecal levels of calprotectin and lactoferrin at the study baseline and end of trail. A clean and screw-top container labeled with patient’s code and the date will be given to each patient for fecal sample collection. Participants will be asked to do fecal sampling in the morning. To decrease the changes in the quantity of bacteria in fecal samples after sampling, samples will be frozen at − 70 °C within 2 h after sampling. To take care of this, we will use three approaches: First, we will ask patients to come to the study lab at the day of stool sampling. All the necessary facilities will be available to do fecal sampling in the lab. Second, if the first approach did not work for a patient, we will ask him/her to bring the sample within2 h to the lab. Third, if he/she was not able to do the second approach, we will ask patients to call the study investigators and then somebody from the team would go the patients’ home and take the sample to the lab. The samples will be kept at − 70 °C until further analysis. Total DNA from stool samples will be extracted using the QIAamp (QIAGEN) commercial fecal DNA kits. In addition, the quantity of butyrate-producing bacteria including *Clostridium* cluster IV, *Faecalibacterium prausnitzii*, and *Roseburia* spp.; prebiotic bacteria including *Lactobacillus* spp. and *Bifidobacteria* spp.; and mucus-degrading bacteria including *Akkermansia muciniphila*, *Bacteroides fragilis, Ruminococcus* spp., as well as *Firmicutes* and *Bacteroidetes*, will be determined using the quantitative real-time polymerase chain reaction (qRT-PCR) which will be done by the LightCycler® 96 SW 1.1 instrument (Roche, Germany). Each reaction mixture contains SYBR Premix Ex Taq II (Takara, China), specific primers, and DNA template. In order to design primers, we will use sequence of primers used in the earlier studies [34, 35]. Selection of taxa was based on their correlation with UC and their effectiveness on gut microbiota balance [36]. It has been proposed that mucus-degrading bacteria have an important role in the etiology of UC which is defined as an intestinal mucosal disorder [36]. Also, most selected bacteria are involved in production of short-chain fatty acids (SCFAs), particularly butyrate, which are important metabolites in maintaining intestinal homeostasis [37, 38]. SCFAs are the important fuel for intestinal epithelial cells, are known to strengthen the gut barrier function, and activate signaling cascades that control immune functions and consequently intestinal inflammation [38]. Based on the previous studies, UC patients not only show reduced levels of SCFAs-producing bacteria in intestinal mucosa and feces, but the actual steady-state levels of SCFAs herein also appear to be less than healthy controls [39, 40]. Furthermore, in most clinical trials on patients with intestinal disorders such as UC or irritable bowel syndrome, these taxa were evaluated [34, 41].

In addition to fecal microbiota, fecal concentrations of calprotectin and lactoferrin will be measured using the ELISA commercial kits. Calprotectin is a calcium binding protein commonly derived from neutrophils and monocytes and in a less extent from macrophages [42]. Calprotectin is found in stool and plasma, and its concentration increases throughout inflammatory conditions, including IBD and infection [43]. Lactoferrin is a glycoprotein expressed by activated neutrophils [44]. This factor is sensitive and specific for detecting inflammation in chronic IBD [44].

### Anthropometric measures

Weight will be measured using a digital scale at the state of minimum clothing without shoes to the nearest 100 g. Standing height will be measured using a standard stadiometer, without shoes, to the nearest 0.5 cm. BMI will be determined as weight in kilograms divided by height in meters squared.

### Blood pressure

Systolic and diastolic blood pressures will be measured twice with a 15-min interval at the right arm using a mercury barometer calibrated by the Institute of Standardization and Industrial Research. Before measurement, patients will be asked to rest for 5 min. The average of two measurements will be considered as participants’ systolic and diastolic blood pressures.

### IBD severity

The severity of IBD will be examined using the 9-point partial Mayo score designed by Sutherland et al. (the questionnaire is available in Supplementary file, section D) [29]. This scale composes of three categories including rectal bleeding (0 = none, 1 = visible blood with stool less than half the time, 2 = visible blood with stool half of the time or more, 3 = passing blood alone), stool frequency (0 = normal, 1 = 1–2 stools/day more than normal, 2 = 3–4 stools/day more than normal, 3 = > 4 stools/day more than normal), and physician assessment (0 = normal, 1 = mild, 2 = moderate, 3 = severe) that each gets 0–3 score. By summing up these scores, we will have a total score of 0–9. Greater scores show higher severity of disease.

### Quality of life

We will use inflammatory bowel disease questionnaire-9 (IBDQ-9) to assess patients’ quality of life (the questionnaire is available in Supplementary file, section E) [45]. This questionnaire comprises 9 items that assess 4 dimensions including bowel and systemic symptoms, emotional status, and social functioning. Each item is scored from 1 to 7. Total score of this questionnaire ranges from 9 to 63; in which greater scores show better quality of life. Prior studies have shown that the questionnaire presents valid and reliable data on quality of life of IBD patients.

### IBD disabilities

To assess IBD-related disabilities, we will apply inflammatory bowel disease disability index (IBD-DI) that contains 28 questions on patients’ health, body functions, body structures and activities, participation, and environmental factors (the questionnaire is available in Supplementary file, section F) [46]. Details on scoring of IBD-DI were elaborated by Leong et al. [47]. The response of each item on the questionnaire is either dichotomous “yes” versus “no” or ordinal on a 1 to 5 Likert scale (1 being no difficulty and 5 being extreme difficulty). Scores from each question are combined to obtain total score of each domain and a final composite score of disability ranging from − 80 (maximum degree of disability) to 22 (no disability) with zero as the anticipated point of neutrality.

### Mental health

Based on previous publications, psychological disorders including depression, anxiety, and psychological distress are prevalent among IBD patients [48, 49]. Depression and anxiety will be screened using the Iranian validated version of Hospital Anxiety and Depression Scale (HADS) which is a brief and useful questionnaire to assess psychological disorders and to measure the symptoms and severity of anxiety disorders and depression (the questionnaire is available in Supplementary file, section G) [50]. It contains fourteen items and consists of two subscales: anxiety and depression. Each item includes a 4-point scale; higher scores indicate an increased level of anxiety and depression. Maximum score is 21 for anxiety and depression. To assess psychological distress, we will use the Iranian validated version of General Health Questionnaire (GHQ) that includes 12-items (the questionnaire is available in Supplementary file, section H) [51]. Each item provides a 4-point rating scale (less than usual, no more than usual, rather more than usual, or much more than usual). To calculate the total score of psychological distress for each participant, we will use the bimodal scoring method (0-0-1-1) [52, 53]. This method gives the total score ranging from 0 to 12; higher scores indicate a greater degree of psychological distress. Overall, our previous investigations revealed that the questionnaires provide relatively valid measures of mental health.

### Adverse events

Patients will be asked to report any adverse events that may have occurred throughout the study. Investigators will record these events.

### Statistical analysis

The Kolmogorov-Smirnov test will be used to examine normal distribution of variables. Log transformation will be conducted for the non-normally distributed data. To examine differences in qualitative variables between soy milk and control groups, we will use the chi-square test. We will apply the independent sample *t* test to detect differences in quantitative variables between the soy milk and control groups. In addition, mentioned test will be used to compare between-group changes in outcome variables. To do within-group comparison, we will use the paired-sample *t* test. Multivariate analysis of covariance (ANCOVA), as a general linear model, will be used to examine the effects of soy milk consumption on outcome variables. In this analysis, baseline value of outcome variables and potential confounding variables which are different between the intervention and control groups will be adjusted to avoid potential risk of bias and detect independent results. All statistical analyses will be done using the SPSS software version 18 (SPSS, Inc. Chicago, IL, USA). *P* < 0.05 will be considered significant.

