### Inclusion criteria

We will include (1) patients with mild to moderate UC, (2) those who are between 20 and 60 years, (3) patients at the remission stage of disease with stable medication therapy, and (4) those with body mass index (BMI) of 18.5–30 kg/m^2^. To determine disease severity, the partial-Mayo scale will be applied. Based on this scale, scores of 3–8 are considered as mild to moderate UC [29].

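### The rule to log-transform any variable that fails a Kolmogorov-Smirnov test cannot be carried out on IBD-DI or on zero partial Mayo scores, both primary outcomes, and it lets the data pick the analysis scale

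*Protocol article*

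**What the plan says.** All of this is in the protocol article.

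- **Statistical analysis:** "The Kolmogorov-Smirnov test will be used to examine normal distribution of variables", followed by "Log transformation will be conducted for the non-normally distributed data". Quantitative outcomes then go to independent t tests (including on between-group changes), paired t tests and ANCOVA adjusted for baseline. No offset, exception or rank-based alternative is named. The section does not say whether the normality test is run by arm, pooled or on residuals, or whether it is corrected for an estimated mean and SD.
- **IBD disabilities:** the IBD-DI composite runs from -80, the worst state, "to 22 (no disability) with zero as the anticipated point of neutrality".
- **IBD severity:** for partial Mayo, "By summing up these scores, we will have a total score of 0–9". Under Inclusion criteria, "scores of 3–8 are considered as mild to moderate UC".
- **Mental health:** for GHQ-12, "This method gives the total score ranging from 0 to 12".
- **Assessment of variables:** IBD severity and disability are listed among the primary outcomes; mental health is secondary.
- **Sample size calculation:** 15 per group, with drop-out of up to 50% allowed for.

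**The concern.** A rule applied to every variable has to be executable on every variable. A logarithm needs a value above zero, and two primary outcomes have stated ranges that reach zero or below. If one of them fails the test, an analyst following the text either loses the patients without a logarithm or improvises an offset or another test after seeing the data. The loss would not be random. For IBD-DI it takes the patients at or below the neutral point, on the disabled side. For partial Mayo it takes the patients who improved to zero; if soy milk worked, more of them would be in the soy milk arm, and the comparison would be biased against it.

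The second issue is that a test of normality in the trial data decides whether each outcome is compared on the raw or the log scale. In samples this small that decision is unstable, so the form of the reported effect (difference or ratio) is not fixed in advance.

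**Working it through.** **1. Can the rule be applied to the stated scales?** log(x) exists only for x > 0.

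| Outcome | Status | Stated range | Values without a logarithm | When they can occur |
|---|---|---|---|---|
| IBD-DI | primary | -80 to 22 | -80 to 0 | both visits |
| Partial Mayo | primary | 0 to 9 (3 to 8 at entry) | 0 | after baseline only |
| GHQ-12 | secondary | 0 to 12 | 0 | both visits |

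For IBD-DI the range spans 22 - (-80) = 102 points, of which 80 (80/102 = 78%) lie below zero. This describes the scale; the article does not say where its patients will fall on it.

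**2. How often does the test flag true skew?** Samples were simulated from a lognormal distribution, with normality tested at 5% using the estimated mean and SD. The log-SD is an assumption, since the article gives no spread for most markers. Results for one sample of n = 15:

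| Assumed log-SD | KS with Lilliefors correction | Uncorrected KS |
|---|---|---|
| 0.5 | 26% | 1% or less |
| 0.75 | 47% | 2% to 3% |
| 1.0 | 66% | 7% to 10% |

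The ranges in the last column come from asymptotic and exact critical values. With 7 to 8 completers per arm (half of 15), Lilliefors flags about 13% to 37% over log-SD 0.5 to 1.0. With 30 pooled, it flags about 49% at 0.5 and 93% at 1.0.

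**3. What does the rule cost in power?** The rule itself has to be simulated: log if the test fails, raw otherwise. Assumptions are lognormal data, log-SD 0.8, a true halving, 15 per arm, and a two-sided 5% t test.

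| Analysis | Power |
|---|---|
| Always raw | 51% |
| Always log | 63% |
| Rule, Lilliefors, pooled 30 | 62% |
| Rule, Lilliefors, log if either arm fails | 63% |
| Rule, uncorrected KS | about 53% to 56% |

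The log is triggered in about 76% of trials (either arm) to 86% (pooled) with Lilliefors, and type I error stays near 5%. At 8 per arm, the Lilliefors rule (either arm) gives about 35%, against 36% to 37% always on the log scale.

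**4. What skew do the article's own figures imply?** The Sample size calculation uses an SD of 141 with means of 424 and 602. If calprotectin is lognormal, log-SD = sqrt(ln(1 + (SD/mean)^2)):

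- 141/424 = 0.333, so log-SD = sqrt(ln(1.111)) = 0.32
- 141/602 = 0.234, so log-SD = sqrt(ln(1.055)) = 0.23

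With these values and 15 per arm, power is about 91% raw and 94% log, and the rule falls between them. The choice of scale therefore costs at most about 3 points.

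**The case against.** The strongest case on the other side has four parts.

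- **The harm is conditional.** IBD-DI must first fail the test, and the analyst must then log a scale that the article itself describes as running below zero. This is right. A reader might infer that the plan will drop the most disabled patients; the text does not support that as a certainty. It does show that the rule has no valid outcome once a score fails.
- **The power loss can be overstated.** A reader might set 51% (always raw) against 63% (always log) and call the gap the cost of the rule. The article does not prescribe always raw. With Lilliefors, the samples that the test misses look near-normal, and the raw t test does adequately in them. A real loss appears only with uncorrected KS, and the article does not say which version is meant. It would also go too far to say that KS simply misses skew at n = 15: with Lilliefors at log-SD 1.0 it finds about two cases in three, and pooling to 30 finds more.
- **Change scores.** A reader might infer that changes, which can be zero or negative for any outcome, will be logged. The article does not clearly say so; taking differences of logged values fits its wording equally well.
- **A condensed article leaves detail to a fuller plan.** That would excuse silence. Here the article states a rule for all non-normal data, and the rule conflicts with the score ranges it gives elsewhere.

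**Conclusion.** The point holds in a limited form. That the log rule cannot be carried out on IBD-DI scores of 0 or below, or on zero scores on partial Mayo and GHQ-12, follows from the article's own ranges and needs no outside assumption. It matters because two of these are primary outcomes and the values lost would depend on the outcome. It takes effect only if the variable fails the test, and for partial Mayo only at the end of the trial.

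That the data choose the scale is also established, but its size rests on assumed skew and on the unspecified version of the test. The power cost is about a point or less with Lilliefors at log-SD 0.8, about 7 to 10 points (63% minus 56% to 53%) with uncorrected KS, and negligible at the skew implied for calprotectin. The case for change rests on an inexecutable rule and a scale not fixed in advance, not on lost power. It should be corrected, but it does not invalidate the design.

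**What to change.** Delete the KS trigger and fix the scale for each outcome in advance:

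- **Laboratory quantities** (calprotectin, lactoferrin, hs-CRP, the cytokines and the qPCR quantities): analyse on the log scale at both visits, with changes taken as differences of logs and results given as ratios.
- **Scores** (partial Mayo, IBD-DI, IBDQ-9, HADS and GHQ-12): analyse untransformed by baseline-adjusted ANCOVA, with a rank or permutation test as sensitivity analysis.

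This changes analysis wording only and needs no extra patients, visits or assays. The downside is that laboratory results are reported as ratios rather than differences in the original units.

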### Study design and intervention

The diagram for Standard Protocol Items: Recommendations for Interventional Trials (SPIRIT) is shown in Fig. 2. After recruiting participants, participants will be stratified based on age (20 to 40 and 40 to 60 years), gender (male/female), BMI (18.5 to 24.9 and 25 to 30), and type of medicines (anti-inflammatory and immunosuppressant) into different blocks and will be randomly allocated to the intervention or control groups. For each patient in a certain block, a matched person in terms of abovementioned variables would be placed in that block. Then, these two patients in a given block would be randomly assigned to the intervention and control groups. To do randomization, an identification code will be given to each eligible patient, and then, code of patients with the same age, gender, BMI, and medication will be stated in the lottery container, and finally, patients with the same conditions will be randomly assigned to the intervention or control groups. Random allocation will be done by a person who is unaware about the aim of our study. Patients in the intervention group (*n* = 15) will receive 250 mL/day preservative-free soy milk along with routine treatments that they were taking for their condition. Participants in the control group (*n* = 15) will receive only routine treatments. The intervention will last for 4 weeks. The assessment of primary and secondary outcome variables will be done at the study baseline and end of trial. Participants in both groups will also receive usual dietary recommendations for IBD patients based on European Society for Parenteral and Enteral Nutrition (ESPEN) guideline [32]. This guideline will be explained to patients by an experienced nutritionist. Given that preservative-free soy milk will be expired within 12 days after production, three 1-L bottles of soy milk will be delivered to patients in intervention group every 12 days (at the study baseline, day 12, and day 24). At the study baseline and day 12, patients in the intervention group will received 3 1-L bottles of soy milk (used during 12 days), and at day 24, they will received 2 1-L bottles of soy milk (used during 8 days). Due to the unfavorable taste of soy milk, patients in intervention group will be asked to consume it at night before sleep. They should consume a 250-mL glass of soy milk every night. Participants will be instructed in a class, prior to the start of trial, about the quantity of soy milk they have to consume in a day. A standard glass (which contained 250 mL soy milk) will be shown to participants, and all will be asked to use the same glass to make sure that the daily portion they are consuming is the one the investigators requested. To control this, participants will be contacted every day and they will be asked to send us the photo of the glass they are using for soy milk drinking. At each delivery of soy milk bottles, patients will be monitored for soy milk consumption and will be asked to give back the empty bottles. Participants’ compliance will be assessed using the following formula: (number of used packages/all given packages) × 100. In addition to assessment of compliance, consumption of soy milk will be monitored by phone call every week. In addition, collecting three 1-day dietary recalls from participants throughout the study can further help computing the compliance to soy milk intake. Participants will be asked not to change their lifestyle, dietary habits, and medicines during the study.

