### Strengths

This is the first clinical trial investigating the effects of soy milk consumption on gut microbiota and inflammatory markers in patients with UC. It must be kept in mind that the intervention is of low cost and can easily be carried out in clinical practice. In this study, patients will be block matched with each other in terms of several variables that might influence the eventual findings. Several outcomes including subjective- and objective-based symptoms along with biochemical indicators will be examined in patients at the study baseline and end of trial. Moreover, compliance to the intervention will be assessed throughout the study.

We hypothesize that soy milk consumption can result in decreased inflammation through inducing changes in gut microbial community. Improvement in gut microbiota and inflammatory markers would lead to beneficial effects on disease symptoms and severity as well as quality of life.

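### Patients are randomised in matched pairs, but the planned t test and the ANCOVA covariate rule normally leave the matching factors out, so the between-group tests are conservative if those factors predict outcome

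*Protocol article*

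**What the plan says.** **Allocation** (Study design and intervention). Four two-level factors define the strata. Age band and sex come first: "participants will be stratified based on age (20 to 40 and 40 to 60 years), gender (male/female"). The other two are listed next to them: "BMI (18.5 to 24.9 and 25 to 30), and type of medicines (anti-inflammatory and immunosuppressant) into different blocks". Pairs are formed inside the strata: "For each patient in a certain block, a matched person in terms of abovementioned variables would be placed in that block". The members of a pair go to opposite arms by lot, as the article puts it: "these two patients in a given block would be randomly assigned to the intervention and control groups". This is 1:1 randomisation within matched pairs.

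**Reason given** (Strengths). The design is presented as an advantage because "patients will be block matched with each other in terms of several variables that might influence the eventual findings". The protocol itself therefore treats the matching factors as possibly prognostic.

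**Analysis** (Statistical analysis). Arms are compared with an independent-samples "test to detect differences in quantitative variables between the soy milk and control groups", and the "mentioned test will be used to compare between-group changes in outcome variables". Pairing appears only for before-versus-after comparisons: "To do within-group comparison, we will use the paired-sample" t test. The ANCOVA takes the baseline value and those potential confounders that turn out to differ between the arms. Pair, block and matching factors are not named in any analysis.

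**The concern.** The analysis should reflect how patients were randomised. Here the stated covariate rule works against the design. Within complete pairs the four categories are identical in the two arms, so they cannot differ, and a rule that admits only variables that differ passes over them. This is a rule the article states, not a detail left to a fuller document.

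If the factors predict outcome, the two members of a pair are positively correlated. An analysis that ignores this still gives an unbiased estimate, but reports a standard error larger than the true one: intervals too wide, a test below its nominal size, and precision wasted. The trial has 30 patients, and the Limitations section says a larger sample is not affordable.

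**Working it through.** **The plan's own figure.** Inputs from Sample size calculation: means 424 and 602 (difference 178), SD 141, multipliers 1.96 and 0.842, drop-out 50%.

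n = 2 × (1.96 + 0.842)² × 141² / 178² = 9.85, so 10 per arm; 10 × 1.5 = 15. The stated 15 is reproduced. The formula is for independent arms. The planning effect is 178/141 = 1.26 SD.

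**The t test on end values.** With n pairs and within-pair correlation ρ, the variance of the difference in means is 2σ²(1−ρ)/n. The unpaired test estimates about 2σ²/n, so its standard error is too large by 1/√(1−ρ). The document gives no ρ, so the values below are assumptions. Matching is on four two-level factors; if nothing else is shared within a pair, ρ = 0.3 requires them to explain 30% of outcome variance.

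Simulation, 60,000 trials per setting, effect 178/141:

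| ρ | SE inflation | Type I error, unpaired, 15 pairs | Power, unpaired v paired, 15 pairs | Power, unpaired v paired, 10 pairs |
|---|---|---|---|---|
| 0 | 1.00 | nominal | 0.915 v 0.895 | 0.763 v 0.711 |
| 0.1 | 1.05 | 0.040 | 0.925 v 0.922 | 0.770 v 0.753 |
| 0.2 | 1.12 | 0.031 | 0.935 v 0.948 | 0.780 v 0.801 |
| 0.3 | 1.20 | 0.022 | 0.947 v 0.970 | 0.797 v 0.852 |
| 0.5 | 1.41 | 0.008 | 0.968 v 0.995 | 0.824 v 0.941 |

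A strict paired t test has n−1 degrees of freedom instead of 2n−2. It gives a narrower interval only if ρ exceeds 1 − (t₂ₙ₋₂/tₙ₋₁)², with t the 97.5% quantiles: about 0.09 for 15 pairs, 0.14 for 10 and 0.21 for 7.

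**The ANCOVA.** Simulation with 15 complete pairs, four binary matching factors, effect 0.8 SD and an assumed baseline-to-end correlation of 0.5 apart from the factors:

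| Variance explained by factors, baseline / end | Type I error, baseline only | Reported / true SE, baseline only | Power, baseline only | Power, baseline + four factors |
|---|---|---|---|---|
| 10% / 10% | 0.043 | 1.02 | 0.70 | 0.70 |
| 0% / 10% | 0.035 | 1.07 | 0.66 | 0.70 |
| 30% / 30% | 0.043 | 1.03 | 0.79 | 0.81 |
| 10% / 30% | 0.031 | 1.11 | 0.73 | 0.81 |
| 0% / 30% | 0.018 | 1.24 | 0.65 | 0.81 |

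Where the baseline carries the factors' effect, adjusting for it recovers nearly everything. The t test on changes behaves similarly: type I error 0.048 at 30% / 30%, 0.025 at 0% / 30%.

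**Cost under drop-out.** Error degrees of freedom with intercept, treatment, baseline and four factors: 30 − 7 = 23; with 20 completers, 20 − 7 = 13; with 14, 14 − 7 = 7. Power at effect 1 SD, baseline-only v baseline plus four factors (ranges cover separate simulation set-ups):

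- 10 per arm, factors explain 10%: 66–69% falls to 61–65%.
- 8 per arm, factors explain 10%: 54–58% falls to 46–48%.
- 10 per arm, factors explain 30% of baseline and end value: 78% falls to 75%.
- 10 per arm, factors explain 30% of the end value only: 64% rises to 75%.

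**The case against.** The strongest reply is that the unpaired t test is not the whole plan. The Statistical analysis section also assigns a baseline-adjusted ANCOVA to the soy milk effect, and with 15 pairs that model loses little when the factors act on the baseline as they do on the end value. This stands. A reader might infer that the whole gain from matching is lost. The documents do not support that: balance and the true precision of the estimate are kept, and the ANCOVA recovers part or most of what the reported standard error would miss.

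A reader might also fix on a single large loss, such as 79% v 86% power at ρ = 0.3 and an effect of 1 SD. That compares two t tests and rests on an assumed correlation and an effect below the planned 1.26 SD. At the planning effect with 15 pairs the gap at ρ = 0.3 is about 2 points, and at ρ = 0.1 there is none.

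It is also fair to say that the matching factors could enter the ANCOVA under the present rule. Only bands are matched, so actual age and BMI may differ within them, and drop-out breaks pairs. Hence the rule normally, not always, leaves them out. Admission would then depend on chance imbalance in the data, which is no substitute for prespecification.

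Finally, adding four terms is not free at the attrition the protocol allows for. This stands too and belongs in the decision.

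**Conclusion.** The mismatch between pair-matched randomisation and the stated analysis is real. Its direction is conservative: nothing here biases the estimate or inflates false positives. For the t test on end values the standard error is inflated by 1/√(1−ρ), with type I error of about 4%, 2% and 0.8% at ρ of 0.1, 0.3 and 0.5 with 15 pairs. For the baseline-adjusted ANCOVA the effect runs from negligible to large (type I error 1.8%, power 65% v 81%), the latter only if the factors explain 30% of the end value and none of the baseline. These sizes rest on assumed correlations, the assumed 0.5 between baseline and end value, and complete pairs. Because no correlation is given, no single figure can be attached to this trial, and at ρ = 0 nothing is lost. The plan should be corrected, but the point does not undermine the trial.

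**What to change.** In Statistical analysis:

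1. Name the baseline-adjusted ANCOVA as the main between-group analysis; the section currently ranks neither it nor the t test.
2. Prespecify in it age group, sex, BMI group and medicine type, whatever the observed imbalance. Alternatively, fit matched pair as a random effect, which keeps patients whose partner has dropped out.
3. Delete the rule that selects covariates because they differ between the arms.
4. Make the unpaired t tests descriptive. Do not replace them with a strict paired t test, which halves the degrees of freedom and discards the partner of every drop-out.

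This changes wording only; no extra data are needed, since the factors are recorded in order to randomise. The statistical price of the four factors is four error degrees of freedom. If drop-out is heavy and the factors are only weakly prognostic, that means about 4 to 5 points of power with 10 completers per arm and 8 to 10 points with 8 per arm. The choice between four fixed terms and a pair effect should therefore be made in advance with the expected attrition in view, not after the data are seen.
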